## **Objectives {7}**

The main aim of this study will be to test the effectiveness of a social norm feedback intervention to reduce the unnecessary prescription of nimodipine by general practitioners within the National Institute of Social Service for Retired and Pensioners (INSSJP-PAMI) in Argentina. As secondary objectives, we will address four additional issues. First, we will assess the effectiveness of e-mails as delivering method of the behavioral intervention. Second, we will evaluate the validity of social norms feedback as a procedure for changing physicians prescriptive practice in the Latin American context. Third, given concerns about possible deterrence effects of communications with strong language or implying potential punitive actions from regulatory agencies, our intervention separates social norm and potential deterrence effects avoiding the use of coercive wording and obviating any mention to potential punishments from authorities. Fourth, we are also interested in knowing more about the acceptability of the intervention from the participants' point of view. For this purpose, a brief post-intervention survey will be implemented. We hypothesize that the treated group will reduce their rates of nimodipine prescriptions in comparison with the control group. We also expect that the intervention will be cost-effective and well accepted by the participants.

139 **Trial design {8}**

140 Pragmatic parallel group randomized controlled trial with two arms (1:1 allocation ratio).

141

142

143 **Methods: Participants, interventions and outcomes**

144 **Study setting {9}**

145 The study will be entirely carried at the National Institute of Social Services for Retired and  
146 Pensioners (in Spanish, Instituto Nacional de Servicios Sociales para Jubilados y Pensionados,  
147 INSSJP). The INSSJP was created in 1971 with the objective of providing universal coverage of  
148 social and health services to the specific needs of the retired and pensioners of Argentina. The  
149 INSSJP is the largest health insurance agency in Argentina and South America, with 5.089.021  
150 affiliates in 2015. Approximately, 65% of the Argentinean citizens older than 60 years old are  
151 affiliates of the INSSJP.

152

153 **Eligibility criteria {10}**

154 The initial study population will be the general practitioners of the INSSJP-PAMI system who  
155 prescribed at least one package of nimodipine during the last quarter of 2018 (n = 8965). The  

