**Outcomes {12}**

The primary outcome will be the cumulative total number of nimodipine prescriptions per 1000 prescriptions of all drugs made by the targeted practitioners during the 6 months after the intervention started.

As secondary outcome, we will estimate the annual monetary savings attributable to our intervention at the national level (for details see Statistical Methods section). Also, we will perform a sub-sample analysis of the physicians that open the e-mails, as informed by the mailer system. Finally, we will assess the acceptability of the intervention through a brief *ad hoc* survey to the intervention arm participants at the end of the study (six months after the start of the intervention).

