**Sample size {14}**

To calculate our minimum sample size, we used GPower 3.1. Power calculation estimated a sample size of 1030 participants for detecting an effect size of  $d=0.05$ , with 80% of statistical power and a significance level of 0.05 in the repeated measures ANOVA.

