**Statistical methods**

**Statistical methods for primary and secondary outcomes {20a}**

The primary outcome will be analyzed using a mixed effects repeated measures ANOVA model. Comparisons between groups will be made using one-way ANOVA, while a multiple linear regression analysis will be implemented to evaluate the predictive value of the group condition controlling for baseline prescription levels. Finally, the Pearson chi-square test will be employed to analyze categorical variables.

To estimate the annual monetary savings attributable to our intervention at the national level, we will make the following calculations: first, we will estimate the number of items that would have been prescribed in the absence of the treatment. This number corresponds to the multiplication of the treatment effect times the number of items prescribed by an average physician in the control group during one year. We then multiply this quantity by the direct average price of each item (in U\$S), according to the registers of the INSSJP-PAMI. This gives an estimated benefit per-physician/year. Should this intervention be implemented for all eligible physicians in the country during a year, *the total estimated benefit* is projected as the product between the benefit per-physician/year and the total number of doctors included in the study in both groups. As opposed to other similar interventions (such as Hallsworth et al., 2016) we will not incur in any substantial per-physician cost, as we will implement our treatment via e-mail instead of post mail. The main cost would thus be related to the analysis of the data to retrieve the top 25% of high-prescribers and the design of the letter. Being conservative, we budget as *total estimated cost* two full-time weeks of work (as we sent two communications) of a public servant for these tasks according to national statistics. Finally, the total estimated cost-benefit of the intervention is the *total estimated benefit* minus the *total estimated cost*.

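### The national saving and net cost-benefit are fixed as bare point estimates with no sampling error carried through, so a positive net figure can be chance alone

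*Protocol*

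**What the plan says.** Protocol, Outcomes {12}, lists the monetary saving first among the secondary outcomes: "we will estimate the annual monetary savings attributable to our intervention at the national level". Objectives {7} attaches an expectation to it: "We also expect that the intervention will be cost-effective and well accepted by the participants".

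Statistical methods {20a} then sets out the whole calculation:

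- The treatment effect is multiplied by the yearly items of an average control physician, then by the average price per item. This gives a benefit per physician per year.
- That benefit is multiplied by the number of doctors in both arms to give the total benefit.
- The cost is a lump sum: "we budget as *total estimated cost* two full-time weeks of work" of one public servant. Per-physician cost is treated as not substantial.
- The result is a difference: "the total estimated cost-benefit of the intervention is the *total estimated benefit* minus the *total estimated cost".

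The section gives no interval, no sensitivity analysis and no condition on the primary comparison. It gives no figure for price, wage, item count or SD. It names three analyses (mixed-effects repeated measures ANOVA, one-way ANOVA, and regression controlling for baseline) without saying which supplies the treatment effect used here, or on what scale.

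**The concern.** An estimated effect is scaled up to national level and set against a cost that stays the same however many doctors are included. The multipliers scale the error of the estimate as much as the estimate itself, but only the estimate is reported. With no true effect, the estimate still favours the e-mails in about half of trials. Whenever it does so by more than the lump-sum cost, the formula returns a national net saving.

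At stake is the policy message. The protocol presents the e-mail as a cheap tool for national use, and defines no other quantity that speaks to cost-effectiveness. A dollar amount without limits will be read as an answer, even when the data are equally compatible with no saving.

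**Working it through.** **The plan's own figures.** The protocol states no monetary result, so there is none to reproduce. The nearest planning figure is in Sample size {14}: "Power calculation estimated a sample size of 1030 participants" for an effect of 0.05, "with 80% of statistical power and a significance level of 0.05 in the repeated measures ANOVA". It can be reproduced as a group-by-time interaction with Cohen's f = 0.05, six measurements and noncentrality f²(N − 2)(m − 1), which gives N = 1030. Other combinations of correlation and number of measurements also give 1030, so the scale of the planned effect is not identified. A plain two-group comparison at a literal d = 0.05 would need 12,560 doctors, and with 1030 it has about 12% power.

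**Inputs from the protocol.** 1:1 allocation; a minimum of 1030 doctors; 8965 prescribers, outliers above the 97.5th percentile removed, then the top 25%. That allows at most 8965 × 0.975 × 0.25 ≈ 2185 doctors before the provider and e-mail checks.

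**Assumed inputs (not in the protocol).** SD of nimodipine items per doctor-year 5 to 80; price US$2 to 20 per item; two weeks' wage US$300 to 2000.

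**Formula.** Treat control-arm items and price as fixed multipliers. The difference in mean items between two arms of N/2 has SE = SD × √(4/N). Multiplying by price and by N gives

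SE(total benefit) = 2 × √N × SD × price.

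With no true effect, P(net > 0) = 1 − Φ(cost/SE). With baseline adjustment, SD is the residual SD.

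**Worked case.** N = 2185, SD 20, US$5: SE = 2 × 46.74 × 20 × 5 ≈ US$9,349. For a cost of US$1000, cost/SE = 0.107 and P = 45.7%. A check with 200,000 simulated trials gave 48.7%, 45.7% and 41.5% for costs of US$300, 1000 and 2000. The 95% half-width of the total benefit is 1.96 × 9,349 ≈ US$18,300, against a cost of at most US$2000.

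| N | SD | Price (US$) | SE (US$) | P, cost 300 | P, cost 1000 | P, cost 2000 |
|---|---|---|---|---|---|---|
| 1030 | 20 | 5 | 6,419 | 48.1% | 43.8% | 37.8% |
| 2185 | 20 | 5 | 9,349 | 48.7% | 45.7% | 41.5% |
| 2185 | 80 | 20 | 149,581 | 49.9% | 49.7% | 49.5% |
| 2185 | 10 | 5 | 4,674 | 47.4% | 41.5% | 33.4% |
| 2185 | 5 | 2 | 935 | 37.4% | 14.2% | 1.6% |
| 1030 | 5 | 2 | 642 | 32.0% | 6.0% | 0.1% |

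With 40–200 items per doctor-year, US$5–15 per item, costs of US$300–2000 and SD 50–100% of the mean, the scenarios computed give 38–50% at N = 1030 and 41–50% at N = 2185. The lower end is 40 items, SD 20, US$5 and US$2000.

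**What drives it.** Only cost/SE matters. P is at least 48% if cost/SE ≤ 0.050, at least 45% if ≤ 0.126 and at least 40% if ≤ 0.253. It falls to 31% at 0.5 and 16% at 1. It stays above 2.5% until the cost reaches 1.96 SE.

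**Baseline adjustment.** Take SD 50, US$5, US$1000 and N = 1030: SE = 2 × 32.09 × 50 × 5 ≈ US$16,047 and P = 47.5%. An assumed baseline correlation of 0.7 shrinks the SD by √(1 − 0.49) = 0.714. Cost/SE rises from 0.062 to 0.087 and P becomes 46.5%.

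**Precision when the e-mails work.** For a single contrast with 80% power at two-sided 0.05, the effect is 1.96 + 0.84 = 2.80 SE. The 95% half-width is then 1.96/2.80 = 70% of the effect, so the gross saving runs from about +30% to +170% of its estimate. If that power refers to 1030 doctors and 2185 are randomised, the half-width is 70% × √(1030/2185) = 48%, giving about +52% to +148%.

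**With limits reported.** With no true effect, the lower 95% limit of net benefit exceeds zero with probability 1 − Φ(1.96 + cost/SE), which is at most 2.5%.

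**The case against.** The strongest reply is that confidence limits on a derived secondary figure are ordinary analysis-plan detail, and that the analysis plan, if there is one, was not available. Nothing in {20a} forbids limits. This has some force, and absence of an interval alone would be a weak point. But {20a} does not defer the calculation: it specifies it down to the wage source and the last subtraction. The point is about what is fixed there.

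Three stronger readings are tempting, and the documents do not support them.

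- A reader might infer that the protocol declares the intervention cost-effective whenever the net figure is above zero. It states no such rule. It says only that savings will be estimated and that cost-effectiveness is expected. Any unbiased point estimate falls on the favourable side of zero in about half of null trials, and the group comparison would be reported alongside.
- A reader might infer that the cost is practically nil, so that a useless e-mail shows a saving in almost half of trials. That holds only if the cost is small against the SE. The protocol gives no price, wage or SD, and low-variance, low-price inputs bring the share down to 1.6% at N = 2185 or 0.1% at N = 1030.
- A reader might take d = 0.05 literally and infer that at the planned effect the interval for the saving runs from a large loss to several times the estimate: 1.96 × 2/√1030 = 0.122, so −144% to +344%. That reading implies about 12% power in an unadjusted two-group comparison and cannot be squared with the stated 80%. It reflects the labelling of the effect size, not the savings formula.

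It is also fair that claiming a saving only when the lower limit exceeds zero is one convention among several.

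**Conclusion.** The point holds in conditional form. As written, the national saving and the net figure are an estimated effect times fixed multipliers, minus a cost that does not grow with the number of doctors. Sampling error is not carried through, and nothing ties the figure to the primary result. A positive net figure under no effect then has probability 1 − Φ(cost/SE): up to almost half if the cost is small relative to the SE of the benefit, about 38–50% under the assumptions of 40–200 items, US$5–15, US$300–2000 and SD 50–100% of the mean, and much lower if item variance or price is low. The protocol's description of the cost points towards a small ratio but does not establish one.

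At an effect the trial can detect with 80% power, the gross saving is uncertain by about 70% either way. That is worth showing, but it does not extend to a loss.

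The matter concerns a secondary outcome and leaves the primary analysis untouched: a cheap improvement, minor in severity.

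**What to change.** In {20a}:

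1. Name the baseline-adjusted treatment effect, and its scale, as the input to the savings formula.
2. Apply the same multipliers to its lower and upper 95% confidence limits, or bootstrap doctors within arm, and subtract the cost from each.
3. Report total benefit and net cost-benefit with that interval. Where the interval includes zero, describe the figure as compatible with no saving.

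Reporting the interval is the essential step; a formal lower-limit rule for claiming savings is optional. The change takes a few sentences and a few multiplications on results already produced, and needs no new data. The downside is that the savings statement becomes less favourable and may be inconclusive.

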**Interim analyses {21b}**

Three months after the first e-mail was sended we will carry an interim analysis to identify the participants of the treatment arm that reached a threshold of 10% reduction of the prescriptions. Those who reach the threshold will receive the “acknowledgement” version of the second e-mail,

meanwhile the remaining participants will receive the “encouragement” version.

#### **Methods for additional analyses (e.g. subgroup analyses) {20b}**

We will perform a sub-sample analysis of the physicians that opened the e-mails, which is a measure of the potential effect that the procedure could have on those actually reached by the intervention.

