156 sample under study will be the high prescribers within that population, defined as the top 25%  
157 prescribers of nimodipine during the last quarter of 2018.

158

159 **Who will take informed consent? {26a}**

160 As in previous similar studies (Hallsworth et al., 2015; Sacarny et al., 2018) the present trial will  
161 not require informed consent from prescribers, since obtaining consent would invalidate the results.  
162 The study did not involve contact or direct intervention on patients, nor access to their personal  
163 information.

164

165 **Additional consent provisions for collection and use of participant data and biological  
166 specimens {26b}**

167 Not applicable

168

169

170

171 **Interventions**

172 **Explanation for the choice of comparators {6b}**

173 The control condition is conceived as a non-specific placebo comparator that replicates the format  
174 of the treatment intervention without its active ingredients (evidence-based information about  
175 nimodipine plus peer comparison). The comparator is supposed to control for non-specific  
176 behavioral factors such as receiving attention or raising awareness about over-prescription as a  
177 general problem in medical practice. Also, the placebo e-mails will allow to check if both groups  
178 open the e-mails at similar rates.

179

180 **Intervention description {11a}**

181 During the intervention phase of the study, participants in the two arms of the trial will receive two  
182 e-mail communications. The messages will be framed as a communicational campaign for  
183 improving the quality of pharmacological practice. In the case of the treatment arm, the first  
184 communication will include two components: a) evidence-based information about the adequate use  
185 of nimodipine and b) the participant's level of prescription of nimodipine compared to their peers.  
186 The second message, 3 months later, will include information on nimodipine prescriptions' change  
187 observed by the participant during the previous quarter ("change" or "no change"). The e-mail  
188 directed to those that reached a relative reduction of 10% of prescriptions compared to their  
189 baseline average will include an acknowledgement of their success intended to work as a verbal  
190 reinforcement of the positive behavior ("acknowledgement version"). The e-mail to the rest of  
191 participants will intend to potentiate the social norm component by stating that many of their  

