**Strategies to improve adherence to interventions {11c}**

The e-mailing system provides an estimation of how many participants open the e-mail, therefore we will consider this estimate as a proxy of the reach of the intervention. Accordingly, non-adherence could be understood as the omission of reading the e-mails. For our primary analysis, we decided to carry out an intention-to-treat approach integrating both the participants who opened the e-mail and those who did not. As a secondary subgroup analysis, we considered separately those participants that opened the e-mail. We have no plans for increasing the opening of the e-mails during the trial.

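### The openers-only analysis is read as the effect in GPs actually reached, but as written it is not a randomised comparison and its comparator and definition of opening are not fixed

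*Protocol*

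**What the plan says.** The protocol's section on adherence {11c} sets the primary analysis: "we decided to carry out an intention-to-treat approach integrating both the participants who opened the e-mail and those who did not". The same section adds: "As a secondary subgroup analysis, we considered separately those participants that opened the e-mail". The Outcomes section {12} lists this sub-sample analysis among the secondary assessments, with opening taken from the mailer. The section on additional analyses {20b} gives its meaning: "We will perform a sub-sample analysis of the physicians that opened the e-mails, which is a measure of the potential effect", with reference to those whom the intervention in fact reached.

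Both arms receive two e-mails. The section on comparators {6b} states one purpose of the control messages: "the placebo e-mails will allow to check if both groups" open at similar rates. The intervention description {11a} says: "The messages will be framed as a communicational campaign for" better drug practice. The treatment e-mails carry nimodipine evidence and feedback on the GP's own prescribing. The control e-mails cover over-prescription in general and then benzodiazepines. Under {11a} and {21b}, the version of the second treatment e-mail depends on whether the GP's nimodipine prescribing fell by 10% at three months.

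No section says whether treated openers are compared with control openers or with all controls. None says whether opening means the first e-mail, either or both.

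**The concern.** Randomisation balances the arms, not the subsets of GPs who later open a message. If the two arms' messages attract different kinds of GP, the opener contrast mixes the intervention's effect with a difference between the people compared. The second e-mail sharpens this. It differs in topic between arms and, within the treatment arm, in version according to the GP's own response. A GP's experience of the first e-mail may also influence whether the second is opened.

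The check on open rates bears on how many GPs open, not on which ones. The planned effect is small (d = 0.05), so modest selection could be of comparable size. At stake is one secondary result that the protocol has already said how to interpret.

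**Working it through.** **Benchmark.** The sample size section {14} gives a "sample size of 1030 participants for detecting an effect size of" d = 0.05, "with 80% of statistical power and a significance level of 0.05 in the repeated measures ANOVA". It does not state the number of measurements m or their correlation. With the noncentral F test for a within-between interaction, lambda = f²·N·m/(1 − rho). Taking f = d/2 = 0.025, m = 3 and rho = 0.8 gives lambda = 0.000625 × 1030 × 3 / 0.2 = 9.66 and power 0.800. The same N arises with f = 0.05, m = 3 and rho = 0.2. So 1030 is attainable but not uniquely determined. It is not in dispute here; d = 0.05 serves only as a yardstick, taken as printed.

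**Illustration with no true effect.** The protocol gives no open rate and no link between opening and prescribing, so every input is an assumption:
- receptivity u is standard normal;
- the nimodipine rate, in SD units, is −0.2·u plus noise;
- logit(open) = b·u, which gives 50% opening for any b;
- b = 0.2 in control, and 0.5 or 0.8 in treatment.

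Mean receptivity among openers is E[u·expit(bu)]/0.5, which is 0.099 (b = 0.2), 0.236 (b = 0.5) and 0.350 (b = 0.8). With baseline-to-follow-up correlation rho and the same link to u at both times, adjustment leaves approximately a fraction 1 − rho of the raw bias.

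| Comparison | b = 0.5 v 0.2 | b = 0.8 v 0.2 |
|---|---|---|
| Openers v openers, unadjusted | −0.2 × (0.236 − 0.099) = −0.027 | −0.2 × (0.350 − 0.099) = −0.050 |
| Same, adjusted, rho = 0.5 | −0.014 | −0.025 |
| Same, adjusted, rho = 0.6 | −0.011 | −0.020 |
| Same, adjusted, rho = 0.8 | −0.005 | −0.010 |
| Same, change from baseline | about 0 | about 0 |
| Treated openers v all controls, unadjusted | −0.2 × 0.236 = −0.047 | −0.2 × 0.350 = −0.070 |

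With equal slopes the opener difference is 0. With the slopes exchanged between arms its sign reverses. Open rates are equal throughout, so the rate check would not detect any of this. A simpler case shows the same: if 20% of one arm's openers are of a different kind, with a mean 0.25 SD apart, the difference is 0.20 × 0.25 = 0.05 SD.

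**Second model.** Suppose opening follows one normal propensity in both arms, with correlation r to the outcome as analysed (after any adjustment). The mean propensity among openers is phi(c)/p, with c = z(1 − p).
- *Openers v openers:* the bias is 0 at equal rates. At 50% v 40% opening it is |r| × (0.966 − 0.798), so 0.05 SD needs |r| of about 0.30. At 60% v 40% it needs about 0.16. If openers tend to prescribe less and the treatment arm opens more, this bias runs against the intervention.
- *Treated openers v all controls:* 0.05 SD needs only |r| of about 0.04 at 30% opening, 0.06 at 50% (0.05/0.798) and 0.10 at 70%.

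**False-positive rate.** A null simulation used 515 GPs per arm (1030 at 1:1), with 50% opening in treatment and 40% in control. For |r| = 0.1, 0.2 and 0.3, rejection at the 5% level was 5.1%, 6.2% and 9.1% for openers v openers, and 17%, 56% and 90% for treated openers v all controls. Intention to treat stayed at about 5%.

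**The case against.** A reader might infer that an opener comparison can never measure the effect in those reached. The documents do not support that. Both arms get e-mails in the same format and within one campaign, opening can be recorded in both, and the content is seen only after opening. If opening of the first e-mail does not depend on arm, treated openers against control openers is a valid comparison with zero bias. This stands. However, the protocol states neither that condition nor what would secure it, such as a common sender and subject line, and it does not confine opening to the first e-mail.

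A reader might also infer that the open-rate check is the only safeguard. The statistical methods section {20a} plans a repeated-measures model and a regression controlling for baseline prescribing, and {13} provides a year of monthly baseline data. {20a} does not tie these models explicitly to the sub-sample, and it also lists one-way ANOVA. But if they are used, stable differences between openers are largely or wholly removed, as the table shows. Selection related to change in prescribing would remain.

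The larger all-controls figures describe a comparison that the protocol leaves open but does not announce. Finally, {20b} speaks of a potential effect and the analysis is secondary, which limits how much weight it carries.

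**Conclusion.** The concern holds in this limited form. A secondary analysis conditioned on a post-randomisation behaviour is given a causal reading that the design supports only if opening is independent of arm. The protocol does not state that condition, and it leaves both the comparator and the relevant e-mail undefined. The primary intention-to-treat result is untouched.

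The size depends on assumptions outside the protocol. In the more adverse scenario above, the bias is about −0.05 SD unadjusted, −0.01 to −0.025 SD with baseline adjustment (correlation 0.8 to 0.5), about 0 on change scores, and about −0.07 SD unadjusted against all controls. A reader might infer that the analysis will show an effect of the planned size where none exists. That does not follow. It would take an unadjusted comparison, selection acting on change, or treated openers set against all controls, and enough selection in each case. The bias can also run in either direction.

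**What to change.** Estimate the effect in those reached as a complier-average effect: two-stage least squares with randomised arm as instrument, opening at least one nimodipine e-mail as exposure (zero in control by design) and the baseline rate as covariate. In essence this is the intention-to-treat difference divided by the treatment-arm open rate; for example, 0.05 SD at 50% opening gives 0.05/0.50 = 0.10 SD.

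State two assumptions:
- An unopened e-mail has no effect.
- The mailer records opening accurately. {11c} calls its figure an estimate and a proxy. If 50% open but only 40% are recorded, the same 0.05 SD becomes 0.05/0.40 = 0.125 SD, so under-recording inflates the result.

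If the sub-sample table is kept, define openers in both arms by the first e-mail only, sent with the same sender and subject line. Compare treated openers with control openers with baseline adjustment, show open rates and baseline prescribing of openers by arm, and label the table exploratory.

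The cost is revised wording, a few lines of code and a wider interval than the naive sub-sample would give. The mailer already supplies the opening data.
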